### Inclusion Criteria

Eligible volunteers for the study must meet all the following items prior to randomization: medicine and dentistry undergraduates in their first to eighth semester, duly enrolled in the institution; aged between 18 and 30 years; and without distinction of sex or gender.

### Exclusion Criteria

Participants will be ineligible for the study if their medical history present psychiatric disorders, neurological trauma, epilepsy, seizures, or drug abuse in the last 6 months (including alcohol); if they are using medication that acts on the central nervous system by self-report or have any metallic implant in the head region; and if they are pregnant or planning to get pregnant in the next 2 months.

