Some studies covering healthy individuals support the hypothesis that TDCS improves performance involving working memories, compared to simulated stimulation (placebo), and these effects can last up to 30 minutes after the end of the session. Nitsche et al [15] proposed general exclusion criteria for TDCS in healthy individuals: individuals must be free from unstable medical conditions or any disease that may increase the risk of stimulation, for example, neurological diseases such as epilepsy or acute eczema under the electrodes. Additionally, they must not have metallic implants near the electrodes. Side effects such as itchiness, a burning sensation, or a headache are common but usually mild and with no long-term impact. Thus, TDCS compares favorably with other therapeutic approaches such as antidepressants or transcranial magnetic stimulation [15].

Noninvasive neuromodulation has emerged as an alternative to replace other forms of treatment such as pharmacological treatments, which although effective, have a high rate of side or adverse effects. Among the different types, neurofeedback and TDCS have shown to be promising approaches that can modify brain wave oscillation and can be used in the development of skills for the self-regulation of brain activity [16]. However, no data were found in the literature associating these two features. The aim of this trial is to investigate the effectiveness of TDCS on the dorsolateral prefrontal cortex (DLPFC) associated with neurofeedback evaluating behavioral and physiological parameters of healthy college students. We hypothesize that there will be a significant increase in declarative memory responses and increased cerebral blood flow using the proposed protocol.

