### Randomization and Blinding

Once eligibility and consent have been approved and completed, randomization will occur using the random list generated by an automated web-based randomization program. Participants will be randomly assigned into 1 of the following 2 groups:

Group A: TDCS active + neurofeedbackGroup B: placebo TDCS + neurofeedback

Participants randomized to receive placebo TDCS will have the opportunity to enroll in an open-label portion of the study upon completion of their participation in the randomized portion of the study.

This process will be carried out by a member of the research team (collaborator 3) who is not involved in the study recruitment or development process.

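### The exclusion list has no skin criterion and no general medical-risk clause, so a volunteer with acute eczema at an electrode site is eligible as written

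*Protocol article*

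**What the plan says.** The Introduction of the protocol article summarises general exclusion criteria that a cited source proposed for TDCS in healthy individuals. The main one is that "individuals must be free from unstable medical conditions or any disease that may increase the risk of stimulation". The examples given are "neurological diseases such as epilepsy or acute eczema under the electrodes". A separate requirement follows: "Additionally, they must not have metallic implants near the electrodes".

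The trial's own rules stand in two short sections of the Methods. Inclusion Criteria asks for "medicine and dentistry undergraduates in their first to eighth semester, duly enrolled in the institution; aged between 18 and 30 years", with any sex or gender. Exclusion Criteria removes people whose medical history shows "psychiatric disorders, neurological trauma, epilepsy, seizures, or drug abuse in the last 6 months (including alcohol"), people who report taking medication that acts on the central nervous system, and those who "or have any metallic implant in the head region; and if they are pregnant or planning to get pregnant in the next 2 months". Neither section refers the reader to further criteria elsewhere.

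The section on TDCS places the anode over F3 and the cathode over the contralateral supraorbital area, using saline-soaked sponge electrodes. It plans 10 sessions of 20 minutes at 2.0 mA over 2 weeks. It names tingling and redness at the electrode site as possible effects, says that headaches and burns may occur rarely, and provides for a daily side-effect questionnaire.

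**The concern.** The Introduction presents one TDCS safety standard, and it concerns healthy people, which is the population this trial aims at. The operative exclusion list follows that standard only in part. Two things are left out: the single skin-related example, and the open-ended clause that would catch unstable or risk-raising conditions nobody thought to name. The article gives no reason for leaving them out.

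What is at stake is participant safety. The intervention passes current repeatedly through the same two patches of skin, and the article itself expects local skin effects. If the list is applied literally, someone with inflamed skin at one of those sites passes screening and is randomized. Staff may of course decline to place an electrode there. That decision would then be made after allocation and case by case, when it could have been settled at entry by a written rule.

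**Working it through.** No formula applies, and the plan gives no figure on this point to reproduce. The check sets the reported standard beside the trial's criteria and then looks for any other text that would close a gap.

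**Reported standard (Introduction) against the trial's list (Exclusion Criteria)**

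- *Epilepsy:* carried over by name. Seizures and neurological trauma are added.
- *Metallic implants:* carried over and widened, from the neighbourhood of the electrodes to the whole head region.
- *General clause on unstable conditions and risk-raising disease:* not carried over as a clause. Several named items put part of it into effect: psychiatric disorders, neurological trauma, epilepsy, seizures, drug or alcohol abuse, and centrally acting medication. A condition outside those names is not caught.
- *Acute eczema under the electrodes:* not carried over. No listed item concerns the skin.

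**Other text that might close the gap**

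- Inclusion Criteria covers course, semester, enrolment, age and sex or gender. It contains no health requirement.
- The aim at the end of the Introduction speaks of "evaluating behavioral and physiological parameters of healthy college students". This describes whom the investigators have in mind. It is not an eligibility rule, and it does not clearly cover a local skin condition in an otherwise well student.
- The daily questionnaire evaluates side effects of stimulation. It is monitoring once sessions are under way, not a screen for entry.

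**Test case.** Take a first-to-eighth-semester dentistry student of 22 with acute eczema on the forehead at the cathode site and none of the listed exclusions. Every inclusion item is met and no exclusion item applies, so the student is eligible as written.

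**Exposure if randomized to active stimulation.** 10 sessions × 20 minutes = 200 minutes at 2.0 mA through the affected site. In the placebo group the device switches off after 20 seconds, so the concern falls mainly on the active group.

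**Effect on the design.** The stated calculation gives 25 per group, 50 in all, and 50 × 1.20 = 60 with the dropout allowance. Inclusion Criteria requires eligibility to be settled before randomization, so a volunteer turned away at screening is replaced by another. The 60, the alpha of .05 and the power of 0.80 are unaffected.

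**The case against.** The strongest case against has three parts.

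First, the Introduction is background. It reports what a cited source proposed, and the investigators never say that they adopt it. That is right. A reader might infer that the protocol contradicts itself, and the text does not support this: no trial rule says that eczema excludes, so there is nothing for the exclusion list to contradict. What remains is that the trial's rule admits someone whom the only TDCS safety standard in the document would turn away.

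Second, naming concrete, checkable conditions is a legitimate alternative to an open-ended clause, and the list does name several. This also stands in part. A reader might infer that the list ignores the general criterion altogether. It does not: much of it consists of particular cases of that criterion, and the implant rule is broader than the source's. The gap is limited to the missing skin item and the missing catch-all.

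Third, the article condenses a fuller protocol, and inspecting the skin before placing an electrode is the kind of handling step that a summary leaves out. This is a good answer to any complaint about an unstated skin check. It is weaker for the eligibility list, which is printed as a specific list and points to nothing further.

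A reader might also go on to ask for renewed screening of placebo participants before the open-label portion, which they may enter "upon completion of their participation in the randomized portion of the study". The documents do not support a finding there. The article gives that portion one sentence and prints no entry procedures, so the absence of a repeat check shows nothing.

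**Conclusion.** The point holds at low weight, as an optional improvement. The printed exclusion list omits both a skin criterion and a catch-all for unstable or risk-raising conditions, so a volunteer with acute eczema at F3 or the contralateral supraorbital area is eligible as written. It is an omission measured against the document's own cited standard, not an inconsistency between two trial rules.

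The number of volunteers concerned cannot be derived from the article. It is probably very small in students aged 18 to 30. Sample size, error rates and validity are not affected.

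The conclusion assumes that the printed list is the complete operative one. If the full protocol has a skin exclusion or a general medical-risk clause, the remaining defect is only that the article does not report it.

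**What to change.** Add one item to Exclusion Criteria, along these lines: *acute eczema or other skin disease or lesion at an electrode site (F3 or contralateral supraorbital area), or any other unstable medical condition or illness that makes stimulation riskier*. The skin part can be checked by looking at the two sites during the eligibility screen. The general part keeps the named conditions as they are and catches what they miss.

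The cost is one extra screening item and perhaps a very few volunteers, who can be replaced before randomization, so the target of 60 stands. The Results section says that enrollment has begun, so the item would have to come in as an amendment and apply to volunteers screened from then on.

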### Assessments

Once eligibility and consent have been approved and completed, volunteers will undergo the Stroop test (based on the study by Campanholo et al [17]). This test consists of two tasks, one for reading and the other for naming the color. In both, the stimuli are color names printed in incongruous colors. The word-reading task gives an indication of reading fluency and serves to establish a benchmark for performance effectiveness relative to the color-naming task. The fact that there is an incongruity between the word name and the ink color causes an interference effect in the color naming. This interference is the Stroop color effect. Tests inspired by the Stroop effect are widely used in neuropsychology to measure individuals’ executive control and concentration [17].

After performing the Stroop test, the participant will undergo an assessment of cerebral blood flow by means of a transcranial Doppler ultrasound examination of the middle cerebral artery. The protocol developed by Rogge et al [18] will be carried out. Color-coded transcranial Doppler ultrasound will be performed in combined color and power mode with an ultrasound system equipped with a 2.5 mHz multifrequency probe transducer. Transtemporal insonation will be performed through the temporal bone window using axial and axial insonation plans and coronal with the participant in the right dorsal decubitus position. No eco-enhancer contrast will be used. Peak systolic and end diastolic pressure velocities will be measured in pulsed wave mode. Flow velocity measurements will be performed without angle correction. The examiner was free to optimize the images by changing the pulse gain and repetition frequencies [18].

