### Outcome Variables

The guiding theme of this study is to use tools or strategies to improve learning and promote better retention. The primary expected result is a greater correctness of answers in two phases of the Stroop test (word reading and color recognition) and a decrease in test execution time.

Secondary variables are based on physiological responses of cerebral blood flow where we expect to find an increase in velocity and systolic and diastolic peaks. This hypothesis is based on functional magnetic resonance studies where the results show an increase in local blood flow after the use of TDCS.

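### Eligibility sets no colour-vision requirement, although one of the two primary Stroop phases is colour recognition

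*Protocol article*

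**What the plan says.** Inclusion Criteria asks for enrolled medical and dental students in given semesters, "aged between 18 and 30 years; and without distinction of sex or gender". Exclusion Criteria covers psychiatric and neurological history and recent substance abuse, then students "using medication that acts on the central nervous system by self-report or have any metallic implant in the head region", and closes with an exclusion "if they are pregnant or planning to get pregnant in the next 2 months". No item in either list concerns vision.

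Outcome Variables names as the primary expected result "greater correctness of answers in two phases of the Stroop test (word reading and color recognition) and a decrease in test execution time". Assessments describes the instrument: "This test consists of two tasks, one for reading and the other for naming the color". It adds: "In both, the stimuli are color names printed in incongruous colors". That section also says that word reading is the reference against which colour naming is judged, and that the interference effect arises in the colour naming. It places the Stroop test after eligibility and consent are settled.

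Table 1 ticks the Stroop and Doppler assessment in the enrolment column as well as later. No section sets a performance threshold, a colour-vision screen or a rule for a participant who has difficulty with the colour task.

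**The concern.** One of the two primary Stroop phases requires the participant to tell ink colours apart, and it is the phase that carries the interference effect. For a student who has trouble distinguishing the inks, errors and slow times in that phase may measure perception instead of executive control, and stimulation may have little or no influence on them. Such a student meets every published criterion and can be randomised.

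With 25 evaluable participants per arm, a few unusual colour-recognition scores can widen the spread, shift an arm mean by chance, or tip the Shapiro-Wilk result that decides between the *t* test and its nonparametric counterpart. Removing these participants after randomisation would be a post hoc choice, so the natural place for the rule is eligibility.

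**Working it through.** **1. The plan's own figure.** Sample gives a 40% difference in proportions, alpha .05, power 0.80 and 25 per arm, without a base rate. Reading the 40% as percentage points, two-sided and without continuity correction, the standard two-proportion formula gives:
- 20% v 60%: 23 per arm
- 25% v 65%: 24
- 30% v 70%: 24
- 40% v 80%: 23

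With continuity correction, 10% v 50% and 50% v 90% both give 25. So 25 per arm is reproducible within two participants for mid-range base rates. The total of 60 is 50 × 1.2. A colour-vision criterion leaves the planned 50 and 60 unchanged.

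**2. How many might be affected.** The documents give no prevalence *p*, so 0.5% to 8% is an assumption. Expected number = 60*p*; chance of at least one = 1 − (1 − *p*)^60.

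| Assumed *p* | Expected of 60 | Chance of at least one |
|---|---|---|
| 0.5% | 0.3 | 26% |
| 1% | 0.6 | 45% |
| 2% | 1.2 | 70% |
| 4% | 2.4 | 91% |
| 8% | 4.8 | 99% |

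Among the 50 evaluable participants, the expected number runs from 50 × 0.005 = 0.25 to 50 × 0.08 = 4.

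**3. Effect on power.** Statistical Analysis plans *t* tests, so take the standardised effect that gives 80% power with 25 per arm (normal approximation): *d* = (1.960 + 0.842) × √(2/25) = 0.792. Let *k* of the 50 be affected.
- Kept in the analysis with no treatment effect: the effect becomes *d*(1 − *k*/50), and power = Φ[2.802 × (1 − *k*/50) − 1.960].
- Dropped: *n* per arm becomes (50 − *k*)/2, and power = Φ[2.802 × √((50 − *k*)/50) − 1.960].

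| *k* of 50 | Kept, no effect | Dropped |
|---|---|---|
| 0 | 80.0% | 80.0% |
| 1 | 78.4% | 79.2% |
| 2 | 76.7% | 78.4% |
| 4 | 73.2% | 76.6% |

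The loss is about 1 to 7 percentage points. It applies to the colour-recognition component and the time it takes, because word reading does not require identifying the ink.

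**4. Chance imbalance.** If exactly three participants were affected, all three would fall in one arm with probability 2 × 0.5³ = 25%. That is conditional on there being exactly three. At *p* = 2%, P(exactly 3 of 60) = 34,220 × 0.02³ × 0.98⁵⁷ ≈ 0.087, and 0.087 × 0.25 ≈ 2%. At 4% and 8% the same product is about 5% and 4%.

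**The case against.** The strongest objection is that this is an omission from a condensed article. Adequate vision is the sort of prerequisite that a test manual or full protocol might carry, and the Stroop version comes from a cited source that is not at hand. This has some weight: a check may exist elsewhere. But eligibility criteria decide who is randomised, and the article lists them item by item, down to planned pregnancy. That is not a detail normally left to an analysis plan.

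A second objection is that Table 1 appears to place a baseline Stroop test before allocation, so trouble with the colours could be noticed in time. The extracted table columns are not fully reliable, but this may be right. It does not close the gap, because nothing says what to do when trouble is noticed.

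A third objection stands in part. A stable deficit is present at both visits and largely cancels in each participant's change, and Sample does frame the effect as performance before and after. However, Statistical Analysis does not say whether the between-group test compares changes or post-intervention scores, and change scores would not restore a treatment effect that a participant cannot show.

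A reader might also infer that the primary endpoint is colour naming alone, that colour-deficient students cannot give a valid primary outcome, or that such students will be randomised. The documents do not support this. Word reading and execution time are also primary. The ink colours are not named, and difficulty depends on the type and degree of deficiency. Whether any such student enters is a matter of chance, at 26% to 99% over the assumed range.

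**Conclusion.** The point holds as a modest design gap. The published criteria admit students whose colour-recognition score may reflect perception, and no section provides a screen or a handling rule. About 0 to 5 of 60 would be affected at an assumed prevalence of 0.5% to 8%. If 1, 2 or 4 of 50 show no treatment effect, power falls from 80% to about 78%, 77% and 73%. These figures rest on the assumed prevalence, on the zero-effect assumption and on a normal-approximation effect of 0.792; none of the three is stated in the documents.

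It would be tempting to conclude that the trial's comparison is biased. It is not systematically so: allocation is random, so affected students fall in either arm by chance. The expected result is noise and some dilution, with a chance imbalance possible in arms of this size.

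**What to change.** Add to Exclusion Criteria: self-reported or known colour-vision deficiency, or uncorrected visual impairment, that prevents naming the ink colours used in the test. Ask it as one question at screening, before randomisation.

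The Results section says enrolment began in July 2022, so for participants already enrolled, record the answer, keep them in the main analysis, and run a sensitivity analysis without those affected.

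The cost is a short amendment and one screening question. A few percent of volunteers become ineligible under the assumed range, and the study population is slightly narrower. The planned sample size does not change.

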### Randomization and Blinding

Once eligibility and consent have been approved and completed, randomization will occur using the random list generated by an automated web-based randomization program. Participants will be randomly assigned into 1 of the following 2 groups:

Group A: TDCS active + neurofeedbackGroup B: placebo TDCS + neurofeedback

Participants randomized to receive placebo TDCS will have the opportunity to enroll in an open-label portion of the study upon completion of their participation in the randomized portion of the study.

This process will be carried out by a member of the research team (collaborator 3) who is not involved in the study recruitment or development process.

### Ethical Approval

In accordance with the Declaration of Helsinki, this study strictly follows ethical principles in research involving human participants. All participants will be informed of the nature of the study and all procedures prior to registration. Following resolution 196/96 of the National Health Council (Brazil), only those who sign the free and informed consent form will be included.

This study was approved by the Ethics and Research Committee of Faculdade São Leopoldo Mandic/Campinas-SP under the opinion number 08051619.1.0000.5374. Furthermore, this study was submitted to the Brazilian Registry of Clinical Trials and approved under the RBR-7zs8b5 protocol (Universal Trial Number U1111-1254-0883).

### Assessments

Once eligibility and consent have been approved and completed, volunteers will undergo the Stroop test (based on the study by Campanholo et al [17]). This test consists of two tasks, one for reading and the other for naming the color. In both, the stimuli are color names printed in incongruous colors. The word-reading task gives an indication of reading fluency and serves to establish a benchmark for performance effectiveness relative to the color-naming task. The fact that there is an incongruity between the word name and the ink color causes an interference effect in the color naming. This interference is the Stroop color effect. Tests inspired by the Stroop effect are widely used in neuropsychology to measure individuals’ executive control and concentration [17].

After performing the Stroop test, the participant will undergo an assessment of cerebral blood flow by means of a transcranial Doppler ultrasound examination of the middle cerebral artery. The protocol developed by Rogge et al [18] will be carried out. Color-coded transcranial Doppler ultrasound will be performed in combined color and power mode with an ultrasound system equipped with a 2.5 mHz multifrequency probe transducer. Transtemporal insonation will be performed through the temporal bone window using axial and axial insonation plans and coronal with the participant in the right dorsal decubitus position. No eco-enhancer contrast will be used. Peak systolic and end diastolic pressure velocities will be measured in pulsed wave mode. Flow velocity measurements will be performed without angle correction. The examiner was free to optimize the images by changing the pulse gain and repetition frequencies [18].

